### Objective

The primary objective of this study is to determine if topical chlorhexidine 0.2% in combination with topical natamycin 5% is superior to topical natamycin 5% alone for treating fungal keratitis, in terms of vision at three months. The secondary objectives are: (1) to determine whether there is a difference between combination chlorhexidine 0.2% and natamycin 5% therapy and natamycin 5% alone for secondary clinical outcomes: infiltrate/scar size, time to re-epithelialisation, positive re-culture rates at one week; and (2) to investigate the effect of the alternative treatments on the Quality of Life of participants.

This trial is a response to the expressed need from both clinicians and patients for a readily available and affordable treatment strategy for fungal keratitis that can improve the likelihood of a good outcome. Our recent work in Uganda has shown promise for chlorhexidine 0.2% as an adjunctive therapy
^
19
^. If chlorhexidine 0.2% eye drops, which are very cheap and easy to prepare (by simple aqueous dilution), in combination with natamycin, are found to be superior to natamycin alone, then this offers a realistic, contextually relevant and sustainable solution for this aspect of the complex problem of fungal keratitis. Therefore, a full-scale trial investigating chlorhexidine 0.2% as adjunctive therapy is warranted to provide the evidence for its use.

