Quality of Life Questionnaires	Participants with confirmed fungal keratitis will undergo additional baseline assessments to evaluate quality of life: 1. **Vision-Related Quality of Life (VRQoL) ^ 26 ^:** The WHO/PBD-VF20 tool will be used to assess visual impairment's impact, including mental well-being, dependency, and social functioning. This 20-question instrument includes subscales on visual symptoms, general functioning, and psychosocial aspects. Responses use a five-point scale, from "very good" to "very bad," with a total score out of 100 (higher scores indicate better VRQoL). This has been used in several vision-related studies ^ 27, 28 ^. 2. **General Health-Related Quality of Life (HRQoL):** The EQ-5D questionnaire and EQ-Visual Analogue Scale will assess general health ^ 29 ^. Additionally, the WHOQOL-BREF tool, developed for low- and middle-income countries ^ 30 ^, will measure four health domains: Physical Health, Psychological Health, Social Relationships, and Environment. It consists of 26 questions scored on a positive scale from 1 (low satisfaction) to 5 (high satisfaction). Domain scores are calculated as the mean of item scores and scaled for comparability with WHOQOL-100. Two separate items address overall quality of life and health perception. Higher scores indicate better quality of life.

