### Outcome assessments

Participants will undergo reassessment at various intervals following enrolment, as outlined in
Table 3. Examinations will be conducted similarly to the baseline assessment. Adherence to treatment and symptoms, including side effects, will be queried and recorded at each follow-up. Trial medication adherence will be monitored by weighing eye drop bottles at specified follow-ups, with resupply provided as necessary. Visual acuity will be measured at each visit, with BSCVA assessed at the three-month follow-up (primary outcome measure). Quality of life questionnaires will be repeated at the final three-month follow-up. Slit-lamp examination and corneal photography will be performed at each visit. In vivo confocal microscopy will be repeated at specified intervals to assess fungal hyphae resolution. If the ulcer has not healed at the one-week follow-up, re-scraping for repeat culture will be conducted. Appointment cards will be provided for follow-ups, and transport costs will be covered for outpatient participants.

**Table 3. T3:** Baseline and follow-up assessment components.

Assessment Item	Baseline	Day 2	Day 7	Day 14	Day 21	Day 60	Day 90
History / Baseline questionnaire	X						
Check treatment adherence		X	X	X	X	X	X
Check for side effects		X	X	X	X	X	X
Visual Acuity – Presenting	X	X	X	X	X	X	X
Visual Acuity – BSCVA	X						X
Contrast Sensitivity	X						X
Slit-lamp Examination	X	X	X	X	X	X	X
Cornea Photography	X	X	X	X	X	X	X
*In vivo* confocal microscopy	X		X	X	X		
Cornea samples (Microbiology/PCR)	X		X				
Quality of Life Tools	X						X

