Perforation and/or TPK and/or conjunctival advancement by three months (slit lamp examination by ophthalmic clinician)	The number of patients requiring perforation repair via Therapeutic Penetrating Keratoplasty (TPK), conjunctival advancement, or experiencing perforation itself by three months will be reported using confidence intervals and descriptive statistics. Since the study is not powered to detect significant differences in perforation or TPK rates, exploratory logistic regression analyses will estimate odds ratios for these outcomes between groups.
Loss of Eye	The proportion of patients requiring surgical removal of the eye (evisceration or enucleation) during follow-up will be described with confidence intervals. Logistic regression will explore treatment arm differences and associated risk factors.
Ocular adverse effects, slit lamp examination by ophthalmic clinician.	TThe occurrence of adverse events will be assessed by Fisher’s exact test. Poisson regression will compare adverse event rates, accounting for multiple events per participant.
Quality of life assessed using: EQ-5D, WHO/PBD-VF20, WHOQOL-BREF	QoL outcomes will be assessed using tools tailored to specific interests ^ 38 ^. Disease-related QoL will be evaluated with the WHO/PBD-VF20 (20-item Vision Function Questionnaire), which assesses the impact of visual impairment on mental well-being, dependency, and social functioning. For general health-related QoL, tools include the EQ-5D questionnaire, EQ-Visual Analogue Scale, and the WHOQOL-BREF. The EQ-5D provides standardized health outcome measures, while the WHOQOL-BREF evaluates four domains: Physical Health, Psychological Health, Social Relationships, and Environment. Scoring details for these tools are provided in Table 2. Comparisons of QoL scores between treatment groups will estimate the effects of chlorhexidine and natamycin. Adjustments will be made for variables like age, sex, socio-economic status, and recent health problems. Logistic, linear, and ordinal logistic regression methods will be employed depending on whether the outcome variables are binary, continuous, or ordered categorical. Mean scores and mean differences in QoL subscales and domains will be compared using t-tests and linear regression.

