Cost effectiveness analysis, using EQ-5D data from 3 months and direct cost data	Direct costs incurred by patients will be collected at the three-month follow-up, with economic costs estimated from EQ-5D data collected at baseline and follow-up. Mean direct costs will be compared between treatment arms using t-tests. Changes in EQ-5D scores from baseline to follow-up will also be analyzed similarly.
Drug adherence	The rate of adherence to treatment protocols will be evaluated using descriptive statistics, comparing compliance between the two treatment arms.

**
*Interim analysis*
**

An independent statistician will conduct an interim analysis after 1/3 of participants complete follow-up. 

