Key eligibility criteria	1. Acute MK characterised by: • Corneal epithelial ulceration >1mm diameter • Corneal stromal infiltrate • Acute inflammation: e.g. conjunctival injection, anterior chamber inflammatory cells, hypopyon. 2. Filamentous fungal hyphae visualised on smear microscopy and/or *in vivo* confocal microscopy. 3. Agree to be randomised to either treatment arm and able to give informed consent 4. Agree to be followed up at 2 days, 1 week, 2 weeks, 3 weeks, 2 months and 3 months 5. Adults (18 years and older)
Study type	Randomised controlled trial
Date of first enrolment	12 May 2021
Target sample size	358
Recruitment status	Recruiting
Primary outcome(s)	Best Spectacle Corrected Visual Acuity (BSCVA) at 3 months by a trial certified optometrist
Key secondary outcomes	1. Time to full epithelial healing (slit lamp examination by ophthalmic clinician). 2. Pin-hole visual acuity in logMAR at 3 months, trial-certified optometrist 3. Scar/infiltrate size at 1 week, 3 weeks and 3 months (slit lamp examination by ophthalmic clinician). 4. Ulcer depth at 1 week and 3 weeks (slit lamp examination by ophthalmic clinician). 5. Hypopyon height at 1 and 3 weeks, (slit lamp examination by ophthalmic clinician). 6. Perforation and/or TPK by three months (slit lamp examination by ophthalmic clinician). 7. Positive culture rate at 1 week 8. Ocular adverse effects at each follow up visit (Day 2, Day 7, Day 14, 3 weeks, 2 months, 3 months), slit lamp examination by ophthalmic clinician. 9. Quality of life (QoL) assessed using: EQ-5D, WHO/PBD-VF20, WHOQOL-BREF (comparison between baseline and QoL measures at 3 months) 10. Cost-effectiveness analysis, using EQ-5D data from 3 months and direct cost data. 11. Drug adherence at each follow up visit (Day 2, Day 7, Day 14, 3 weeks, 2 months, 3 months) whilst the patient is using study medications.

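### The cost-effectiveness row in Table 4 assigns EQ-5D to the cost side and plans two separate comparisons that never relate cost to effect

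*Protocol article*

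**What the plan says.** Table 5 of the protocol article lists this outcome as item 10 of 11 key secondary outcomes: "Cost-effectiveness analysis, using EQ-5D data from 3 months and direct cost data". The matching row of Table 4 (Analysis plan) gives the method in three steps.

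- **Data:** "Direct costs incurred by patients will be collected at the three-month follow-up", with "economic costs estimated from EQ-5D data collected at baseline and follow-up".
- **Analysis of cost:** "Mean direct costs will be compared between treatment arms using t-tests".
- **Analysis of EQ-5D:** change from baseline is to be handled in a similar way.

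Elsewhere the article describes EQ-5D purely as a health instrument. Table 2 (Baseline assessment) says: "The EQ-5D questionnaire and EQ-Visual Analogue Scale will assess general health". The quality-of-life row of Table 4 says: "The EQ-5D provides standardized health outcome measures".

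On who supplies what, Randomisation and masking has the randomisation administrator store and dispense the study drugs. Outcome assessments adds that drug is resupplied when needed and that "transport costs will be covered for outpatient participants".

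**The concern.** A cost-effectiveness analysis needs three things: a cost for each arm, an effect for each arm, and a measure that puts the two differences together. The Table 4 row is faulty on each. It draws economic costs from an instrument that holds no resource use and no prices. It names patients as the only source of cost, although the arms differ by a drug that the trial itself hands out. It then stops at two separate between-arm comparisons.

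The result would feed a policy argument. The Objective section presents the trial as a response to an "expressed need from both clinicians and patients for a readily available and affordable treatment strategy", and says that a superior combination would offer a sustainable solution, partly because chlorhexidine costs little. If the combination raised both cost and utility, the planned analysis could not say whether the gain was worth the cost. The cost difference itself might also lack the cost of the added drug.

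**Working it through.** The article gives no cost, price, utility, QALY or threshold, so there is no figure to reproduce. The check sets the passages side by side and writes out what each quantity would contain.

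**1. Can EQ-5D give a cost?** Table 2 and the quality-of-life row of Table 4 both describe it as a health measure. The cost-effectiveness row makes it the source of economic costs. Turning health loss into money would need a valuation step, and the row states none. The economic costs it names also appear in neither of the two comparisons that follow.

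EQ-5D can supply the effect. Take utilities U0 at baseline and U3 at three months (0.25 year), joined by a straight line:

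QALY = 0.25 × (U0 + U3) / 2 = 0.125 × U0 + 0.125 × U3

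Adjusted for U0, the between-arm QALY difference is 0.125 times the adjusted difference in U3. Table 3 schedules the quality-of-life tools at baseline and day 90, so both inputs are already collected. The Table 4 row title and the Table 5 entry refer to EQ-5D from three months only, while the row's text uses baseline as well. The calculation above needs both time points.

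**2. Do the two comparisons give cost-effectiveness?** Write ΔC for the cost difference, ΔE for the effect difference and λ for the value placed on one unit of effect. The net benefit is λ × ΔE − ΔC, with variance

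λ² × Var(ΔE) + Var(ΔC) − 2λ × Cov(ΔE, ΔC)

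A t-test on costs and a separate comparison of EQ-5D change address ΔC and ΔE one at a time. Neither supplies Cov(ΔE, ΔC), and the row does not combine them. A reader could divide one published difference by the other, but could not attach a valid uncertainty to the result.

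**3. What does the cost difference contain?** Assume that participants do not pay for study drug. With p for unit price and q for mean quantity supplied per participant:

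- Planned: ΔC(patient)
- Including study drug: ΔC(patient) + p(chlorhexidine) × q(chlorhexidine) + p(natamycin) × [q(natamycin, combination) − q(natamycin, alone)]

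Trial treatment arms and Dosing schedule give both arms natamycin from the same source on the same regimen. The last term is therefore near zero unless treatment duration differs between arms. What remains is the chlorhexidine term, which is positive. The article gives neither p nor q, so it cannot be sized. The Objective section calls chlorhexidine cheap and simple to prepare, which points to a small value.

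**The case against.** The strongest reply is that this is one row of a condensed article. The row title pairs EQ-5D with direct cost data, and the last sentence treats EQ-5D change as an outcome, so the clause on economic costs may be loose wording for the effect side. Perspective, unit prices and an incremental measure commonly sit in a full protocol or health-economic plan. The sentence on the t-test says mean direct costs, and Table 5 says direct cost data, neither limited to patients.

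Part of this stands. The perspective and the absence of a price list would not be findings on their own, and the row does not say that drug or provider costs are excluded. The missing drug cost is therefore a probable consequence, not a stated one.

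The reply does not rescue the rest. The EQ-5D clause is a positive statement and is wrong as printed. The row also does not defer its method: it names one, and that method does not produce the quantity in its title.

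A reader might go further and infer that all drug cost is left out, or that the arms would look cost-equal for that reason. The documents do not support this. They never say outright that study drug is free to participants; that is inferred from dispensing and resupply. Natamycin largely cancels between arms. Transport cover is stated for outpatients only, and applies in both arms. Nor is affordability the whole reason for the trial. The primary objective is vision at three months, and cost-effectiveness is not among the secondary objectives listed in the Objective section.

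**Conclusion.** The concern holds, within limits. As written, the row puts EQ-5D on the wrong side of the evaluation and specifies an analysis that cannot give the cost-effectiveness outcome listed in Table 5. Both conclusions rest on the printed text alone.

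The added chlorhexidine cost is probably missing from the cost difference. That rests on two assumptions: that participants do not pay for study drug, and that no cost source exists beyond the one named. The size is unknown and may be small.

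This affects one key secondary outcome. The primary analysis and the sample size are untouched. It should be corrected before the economic results are analysed.

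**What to change.** Reword the Table 4 row, and align its title and the Table 5 entry with it, along these lines:

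- **Effect:** EQ-5D at baseline and three months gives the utility or QALY difference between arms, adjusted for baseline utility.
- **Cost:** direct cost data plus study-drug cost, taken as unit price × quantity supplied. State the perspective, and whether reimbursed transport is counted.
- **Analysis:** report incremental cost and incremental effect jointly, with bootstrap uncertainty that resamples each participant's cost and effect together. This needs no willingness-to-pay threshold. Net monetary benefit would need one, and the article gives none.

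The alternative is to rename the outcome as a comparison of patient-incurred costs and EQ-5D change, and to draw no cost-effectiveness conclusion from it. That costs only wording.

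The full version costs a unit-price list and modest extra analysis. Quantities need care. The article describes stock reconciliation on recruitment days and weighing of bottles at specified visits, but does not show that bottles supplied are recorded per participant. Where supply records are lacking, quantity can be estimated from the regimen, and the result reported as approximate because later treatment is adjusted to clinical response. Inpatient and procedure costs should be added only if those data are already collected.

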### Patient and Public Involvement

Pre-study discussions in Tanzania and Uganda highlighted delays in care-seeking for fungal keratitis due to treatment costs, availability, and perceived inefficacy
^
36,
37
^. Community health workers emphasized the need for further training and governmental support to enhance care delivery. 

## Ethics and consent

This work will adhere to the tenets of the Declaration of Helsinki. Ethics committee and regulatory review and approval have been obtained from the Kilimanjaro Christian Medical University College Moshi, Tanzania (approval number 2431) (Date of approval: 14/08/2019); Mbarara University of Science and Technology, Mbarara, Uganda (approval number MUREC 1/7) (Date of approval:05/09/2019); National Institute for Medical Research, Dar es Salaam, Tanzania (approval number NIMR/HQ/R.8a/Vol. IX/3091) (Date of approval: 14/05/2019); Uganda National Council for Science and Technology, Kampala, Uganda (approval number HS 2514)(date of approval: 05/08/2019); the National Drug Authority, Kampala, Uganda (approval number CTC - 0138/2020); the Tanzania Medicines and Medical Devices Authority, Dodoma, Tanzania (approval number TMDA0019/CTR/0024/02); and the London School of Hygiene and Tropical Medicine Ethics Committee, UK (approval number 14908) (Date of approval: 04/04/2018). The study is registered with ISRCTN (87195453,
Table 5). The trial Sponsor is the London School of Hygiene and Tropical Medicine. Any protocol modifications will be submitted for review. Patients requiring continued care post-study will receive treatment at study centers. Results will be presented at scientific meetings and published in peer-reviewed journals.

**Table 5. T5:** Registration Data and Protocol Summary.

Data category	Information
Primary registry and trial identifying number	ISRCTN Registry; ISRCTN87195453
Date of registration in primary registry	27 August 2020
Secondary identifying numbers	
Source(s) of monetary or material support	Wellcome Trust
Primary sponsor	London School of Hygiene and Tropical Medicine (LSHTM)
Secondary sponsor(s)	
Contact for queries	[name] PhD FRCOphth ( [contact])
Title	A comparison of two treatment regimes for the treatment of fungal eye infections in East Africa
Countries of recruitment	Tanzania and Uganda
Health condition(s) or problem(s) studied	Fungal keratitis
Intervention(s)	Participants will be randomised to either topical natamycin 5% plus chlorhexidine 0.2% or topical natamycin 5% alone
Key eligibility criteria	1. Acute MK characterised by: • Corneal epithelial ulceration >1mm diameter • Corneal stromal infiltrate • Acute inflammation: e.g. conjunctival injection, anterior chamber inflammatory cells, hypopyon. 2. Filamentous fungal hyphae visualised on smear microscopy and/or *in vivo* confocal microscopy. 3. Agree to be randomised to either treatment arm and able to give informed consent 4. Agree to be followed up at 2 days, 1 week, 2 weeks, 3 weeks, 2 months and 3 months 5. Adults (18 years and older)
Study type	Randomised controlled trial
Date of first enrolment	12 May 2021
Target sample size	358
Recruitment status	Recruiting
Primary outcome(s)	Best Spectacle Corrected Visual Acuity (BSCVA) at 3 months by a trial certified optometrist
Key secondary outcomes	1. Time to full epithelial healing (slit lamp examination by ophthalmic clinician). 2. Pin-hole visual acuity in logMAR at 3 months, trial-certified optometrist 3. Scar/infiltrate size at 1 week, 3 weeks and 3 months (slit lamp examination by ophthalmic clinician). 4. Ulcer depth at 1 week and 3 weeks (slit lamp examination by ophthalmic clinician). 5. Hypopyon height at 1 and 3 weeks, (slit lamp examination by ophthalmic clinician). 6. Perforation and/or TPK by three months (slit lamp examination by ophthalmic clinician). 7. Positive culture rate at 1 week 8. Ocular adverse effects at each follow up visit (Day 2, Day 7, Day 14, 3 weeks, 2 months, 3 months), slit lamp examination by ophthalmic clinician. 9. Quality of life (QoL) assessed using: EQ-5D, WHO/PBD-VF20, WHOQOL-BREF (comparison between baseline and QoL measures at 3 months) 10. Cost-effectiveness analysis, using EQ-5D data from 3 months and direct cost data. 11. Drug adherence at each follow up visit (Day 2, Day 7, Day 14, 3 weeks, 2 months, 3 months) whilst the patient is using study medications.

Any patients who may be eligible to participate will be given a participant information sheet and its contents will be read out to them by a study team member. They will be asked if they would be willing to participate, which involves being randomised to alternative treatment arms and to be followed-up for three months. The patient will then have the opportunity to discuss any questions that they might have. If the patient would like to participate, they will be asked to read and sign or place a thumb print on the study consent form. The consent will be witnessed by the clinic nurse by a signature on the form. For patients who are unable to read the documentation a second witness who is unrelated to the study will be required.

## Data Availability

No data associated with this article LSHTM Data Compass: Appendix files for "Randomised controlled trial of topical combination therapy chlorhexidine 0.2% and natamycin 5% versus topical natamycin 5% alone for fungal keratitis in East Africa".
https://doi.org/10.17037/DATA.00004598
^
39
^. Appendix1-PIS_consent-East_Africa_2 Appendix2-Monitoring_for_harm Appendix3-Biological_specimens Appendix4-Spirit_checklist Data are available under the terms of the
Creative Commons Zero "No rights reserved" data waiver (CC0 1.0 Public domain dedication).
